# A study protocol for comparing the treatment of varicose tributaries either concomitantly with or separately from endovenous laser ablation of the incompetent saphenous trunk (the FinnTrunk Study). A multicenter parallel-group randomized controlled study

**DOI:** 10.1371/journal.pone.0285823

**Published:** 2023-05-23

## Abstract

**Background:**

Opinions on the treatment of varicose tributaries in relation to saphenous ablation in varicose disease vary. Moreover, the possible role of the tributaries regarding the recurrence of varicose disease remains unclear. The aim of the FinnTrunk study is to compare two different treatment strategies for varicose disease in a randomized setting. In group one, the initial treatment will entail endovenous laser ablation (EVLA) of the incompetent saphenous trunk without tributary treatment. In group two, the varicose tributaries will be treated with ultrasound-guided foam sclerotherapy (UGFS) concomitantly with truncal ablation. The primary outcome measure is the need for additional procedures during the follow-up. The secondary outcome measures are the cost of treatment and recurrence of varicose disease.

**Methods:**

Consecutive patients with symptomatic varicose disease (CEAP clinical class C_2_–C_3_) will be screened for the study. Patients who fulfil the study criteria and give their informed consent will be scheduled for the procedure and randomized to either study group. Patients will be followed-up at 3 months, 1 year, 3 years, and 5 years. The post-procedure pain score based on a numeric rating scale (NRS) and also the use of analgesics, as well as possible procedure-related complications will be recorded at 3 months. Patient-reported outcome measures (PROMs) will be recorded at 1 year. Data pertaining to the additional treatment of varicose tributaries, the Aberdeen Varicose Vein Questionnaire (AVVQ), the Venous Clinical Severity Score (VCSS), and the health-related quality of life (EQ-5D-5L) will be collected at each follow-up visit. A duplex ultrasound (DUS) examination will be performed at each visit, and data on varicose tributaries and the need for additional treatment will be recorded.

**Trial registration:**

Registered on ClinicalTrials.gov, ID NCT04774939.

## Introduction

Varicose veins are common [1], and they can be responsible for various symptoms [2], which can be bothersome to the patient and cause them to seek treatment. The most frequent hemodynamic abnormality in primary varicose disease is reflux of the great saphenous vein (GSV), the anterior accessory saphenous vein (AASV), or the small saphenous vein (SSV) [3–5]. When present, saphenous reflux is considered the primary target of treatment [6], with endovenous thermal ablation and cyanoacrylate closure being the preferred treatment modalities [7–11]. Varicose tributaries connected to the incompetent saphenous trunk can be treated with phlebectomy or ultrasound-guided foam sclerotherapy (UGFS), either concurrently with the truncal ablation (combined approach), or as a separate procedure (staged approach) [12].

Both of the abovementioned approaches have their advantages [12], and both have been associated with good outcomes and low complication rates in the clinical setting, and also in the research setting [13]. However, there is a paucity of randomized controlled trials that have addressed the treatment of varicose tributaries in relation to truncal ablation [14–16], and much of the evidence for the combined approach recommended by the European and American clinical practice guidelines [10, 11] comes from registry data, which may be incomplete and susceptible to bias [6, 17]. Furthermore, not all patients would need, or for that matter want, their varicose tributaries to be treated, if their symptoms could be or had already been adequately eliminated by truncal ablation alone [10, 11, 15, 16, 18, 19].

The aim of the FinnTrunk study is to compare the outcomes of two different treatment strategies for varicose disease. Patients will be randomized to either endovenous laser ablation (EVLA) of the incompetent saphenous trunk alone, or EVLA of the saphenous trunk in combination with UGFS of the varicose tributaries. Patients will be followed for up to five years. The primary outcome measure will be the need for additional treatment of the varicose tributaries during the follow-up, as judged by the patient. The secondary outcome measures will be the cost of treatment and recurrence of varicose disease.

## Methods

### Study design and data management

The FinnTrunk study is a non-blinded, multicenter, parallel-group, randomized, controlled study, which will be conducted in four large Finnish hospitals (Helsinki University Hospital, Oulu University Hospital, Satasairaala hospital in Pori, and Turku University Hospital). The participating hospitals were selected based on the high volume of endovenous procedures in their respective vascular surgery units. Data will be collected by study investigators at each participating center and uploaded to an electronic data capture system (REDCap, Vanderbilt University, Nashville, TN, USA) hosted by and at Helsinki University Hospital. The FinnTrunk study was registered on ClinicalTrials.gov on 24 February 2021 (study identifier NCT04774939), and the first patient was entered in the study register on 6 October 2021. The first study results will be published in a peer-reviewed journal in 2024.

### Aims of the study

The aim of the FinnTrunk study is to compare two different treatment strategies for varicose disease. More specifically, the aim is to evaluate the possible benefits of the combined approach (EVLA of the incompetent saphenous trunk with concomitant treatment of its varicose tributaries by UGFS) and compare it to the staged approach (EVLA of the saphenous trunk as a stand-alone therapy and then UGFS of the varicose tributaries at follow-up visits as necessary). The study questions are listed in Table 1.

**Table 1 pone.0285823.t001:** Study questions.

**The main study question** • Is thermal ablation of an incompetent saphenous trunk adequate as a stand-alone treatment in varicose disease, or do the varicose tributaries also need to be treated in the same procedure? **The questions used to approach the main question** • Does treating varicose tributaries concomitantly with saphenous ablation have an impact on the short-term results of the treatment? • What proportion of the patients whose varicose tributaries that have or have not been treated concomitantly will need further treatment of their varicose disease? • Is the timing of the tributary treatment important in relation to the quality of life of the patient? • Is the tributary treatment or its timing important in relation to the longer-term outcomes or recurrence of varicose disease? • Does the selected treatment strategy have an effect on the treatment costs?

### Study setting and patient screening

Consecutive patients referred to the participating vascular surgery units with symptomatic varicose disease in one leg will be screened for the study by clinical assessment and duplex ultrasonography (DUS). The study inclusion and exclusion criteria are listed in Table 2.

**Table 2 pone.0285823.t002:** Inclusion and exclusion criteria.

**Inclusion criteria** • Age of patient 18–80 years. • Symptomatic varicose disease in one leg (designated as the study leg). • CEAP clinical class C_2_¬–C_3_ (or C_4c_), with the provision of recruiting patients in the clinical classes C_4a_–C_4b_ later in the study, if necessary (slow recruitment); CEAP etiologic, anatomic, and pathophysiologic class E_p_ A_s,d_ P_r_ [20]. • Incompetent great saphenous vein (GSV) and/or anterior accessory saphenous vein (AASV) or small saphenous vein (SSV) in the study leg, which is suitable for treatment with EVLA. • Varicose tributaries connected to the incompetent saphenous trunk. • No prior venous procedures on the study leg. • Palpable posterior tibial artery (PT) or dorsalis pedis artery (DP) pulse / If not: ankle-brachial index (ABI) >0.75. **Exclusion criteria** • Body mass index (BMI) ≥35. • Moderately or severely symptomatic (NYHA class III–IV) congestive heart failure (CHF). • Patent foramen ovale (PFO). • Significant lymphedema of the study leg. • Prior deep vein thrombosis (DVT) or thrombosis of the muscular veins in the calf of the study leg, or pulmonary embolism (PE). • Extensive deep vein reflux in the study leg. • Venous disease of the contralateral leg, for which treatment is indicated. • Pregnancy or lactation, or patient planning pregnancy within the following 6 months. • Known thrombophilia. • Known allergy to lidocaine or a sclerosant.

#### Clinical assessment

‘Symptomatic’ designates symptoms that can be attributed to varicose disease. Examples of such symptoms include pain or aching (or a comparable symptom, e.g., heaviness or tiredness) and edema of the leg, which typically manifest over the course of the day while the patient is prone; cramps and restless legs (these symptoms can also manifest at rest during night-time); in addition to tingling, numbness, and itching. The inclusion criteria do not define which of these symptoms the patient should present with or how disturbing the symptoms should subjectively be for the treatment to be considered indicated. The decision to treat will be left to the discretion of the clinician in charge of the patient, who will assess whether the entirety of the clinical picture (symptoms, clinical signs, and DUS findings) is such that the patient, according to the clinician’s experience, would benefit from the treatment.

The study will primarily recruit patients with unilateral symptomatic varicose disease, and the symptomatic leg will be designated as the study leg. However, patients with bilateral disease where the contralateral leg also has varicose veins or lesser findings of chronic venous disease (telangiectasias or reticular veins) may also be recruited, if treatment of the contralateral leg is not deemed to be indicated by either the patient (based on the symptoms) or by the clinician (based on other indications for treatment, such as skin changes). The presence of the aforementioned symptoms in the contralateral leg will be allowed, provided that the pain attributable to venous disease or the symptoms comparable to pain (*other discomfort* in the Venous Clinical Severity Score [VCSS] [21]) are only occasional (VCSS 1 mild pain) and any edema of presumed venous origin is limited to the foot and ankle (VCSS 1 mild edema). Moreover, varicose veins in the contralateral leg must be few and scattered (VCSS 1 mild varicose veins). If there are multiple varicosities in the contralateral leg, they must be confined to the calf *or* the thigh (VCSS 2 moderate varicose veins).

A patient will not be recruited into the study, if in their contralateral leg they have varicose disease requiring treatment, as deemed necessary by the patient or the clinician in charge of the patient. Furthermore, a patient will not be recruited into the study, if the pain or symptoms comparable to pain in the contralateral leg occur daily (VCSS ≥ 2), the edema extends above the ankle (VCSS ≥ 2), or there are multiple varicosities that involve *both* the calf and the thigh (VCSS 3). DUS of the contralateral leg will not be mandatory.

#### Duplex ultrasonography (DUS)

The protocol for the DUS examination follows previously published recommendations [22, 23]. During the examination, the patient will remain in the standing position with their weight on the opposite leg and with the leg under investigation relaxed. Reflux in the vein will be preferentially elicited by a pneumatic cuff, but manual compression is also allowed. The cut-off value for reflux will be 0.5 seconds in the saphenous veins and 1 second in the deep veins [10, 11, 24]. The US probe will be held longitudinally to the vein being investigated, as the longitudinal view is more accurate for assessing reflux than the transverse view [22]. The following veins and junctions will be assessed for reflux: the common femoral vein (CFV), the popliteal vein (PV), the saphenofemoral junction (SFJ), the saphenopopliteal junction (SPJ), the great saphenous vein (GSV) in the thigh, the anterior accessory saphenous vein (AASV), the small saphenous vein (SSV); and any other veins as indicated.

As stated in the inclusion criteria, the patient must have reflux in the GSV and/or AASV, or in the SSV, to be eligible for the study. Additionally, the reflux must originate at the usual anatomical junction of that vein with the deep vein, i.e., the SFJ for the GSV and the SPJ for the SSV. If the most proximal refluxing saphenous vein in the thigh is the AASV that joins the GSV at or distally to the SFJ, then the reflux may originate at the SFJ or at the junction of the AASV with the GSV. If the AASV has a separate junction with the femoral vein, the reflux must originate at that junction.

The diameter of the GSV will be measured at three points: 3 cm distal from the SFJ, at the mid-thigh level, and at the level of the knee joint. The SSV will be measured at two points: 3 cm distal from the SPJ and at the mid-calf level. In keeping with the frequently shorter course of the AASV, it will be measured at one point, regarded as representative of the vein diameter. The US probe can be held either longitudinally or transversally during these measurements. All three saphenous trunks will be assessed and the diameter, patency, and possible reflux of both the GSV and SSV will be recorded for all study patients. The corresponding parameters for the AASV will be registered only when it is the target for ablation.

Perforating veins will not be systematically searched for or recorded, as there is no agreement regarding their significance in uncomplicated venous disease and their treatment in this setting is rarely considered to be indicated [25, 26].

Extensive deep vein reflux will be defined as reflux of *both* the CFV and PV.

### Patient enrolment and randomization

The patients who fulfill the study criteria will be given a brief information letter and offered the possibility to participate in the study. The baseline characteristics of the patients who give their written informed consent will be recorded in the study register. The patients will fill in the Aberdeen Varicose Vein Questionnaire (AVVQ) [27] (with question 1 omitted [28, 29]) and the EQ-5D-5L, while the investigator will ascertain and record the patient’s Venous Clinical Severity Score (VCSS) [21], Venous Disability Score (VDS) [30], and the clinical class of the Clinical-Etiology-Anatomy-Pathophysiology (CEAP) classification [20], in addition to recording the location and extent of the varicose tributaries.

The patients will be randomly allocated with the REDCap to one of the two study groups before the procedure. Patients in group one will be treated with EVLA of the incompetent saphenous trunk without treatment of the varicose tributaries. Patients in group two will be treated with UGFS of the varicose tributaries concomitantly with the EVLA.

If the patient wishes to decline participation in the study, they will be treated according to the usual regime of the unit.

### Interventions

A diode laser (Leonardo^®^ Dual 45 or Ceralas^®^ E) with a wavelength of 1,470 nm and equipped with a radial fiber (ELVeS^®^ Radial^®^ 2ring Fiber, ELVeS^®^ Radial^®^ 2ring slim Fiber, or ELVeS^®^ Radial^®^ Fiber) (biolitec^®^ AG, Vienna, Austria) will be used for the EVLA. The procedure will be performed under DUS guidance and according to the manufacturer’s instructions, and the goal will be to treat the longest segment of the incompetent saphenous trunk as feasible, taking into account the anatomical relationships of the vein with the nearby sensory nerves and other aspects of patient safety. Accordingly, the GSV will be cannulated for EVLA in the thigh or in the proximal third of the calf, the SSV will be cannulated in the proximal half of the calf, and the AASV will be cannulated in the thigh. The length of the treated vein will also be recorded.

In brief, the target vein will be cannulated percutaneously, and the laser fiber will be advanced in the vein to approximately 1 cm distal from the junction with the deep vein. Perivenous tumescent anesthesia (NaCl 500 ml + lidocaine 1% cum adrenalin 50 ml + sodium-bicarbonate 7.5% 10 ml) will be infiltrated around the vein, and the position of the fiber tip will be verified. The patient will be positioned in the Trendelenburg position during the withdrawal of the fiber, and the speed of withdrawal will be adjusted to reach a linear endovenous energy density (LEED) of approximately 70 J/cm. The patients allocated to group 2 (concomitant UGFS) will be treated with 1% polidocanol (Aethoxysklerol^®^, Kreussler Pharma, Wiesbaden, Germany) foam (1 ml of sclerosant mixed with 3 ml or air) after the laser ablation. The volume of foam will be limited to 20 ml. The patency of the deep veins will be verified by using US after the procedure.

The puncture sites will be covered with adhesive pads, which the patient can remove on the following day. A thigh-length class II compression stocking will be applied, and the patient will be instructed to wear the stocking for 1 week post-procedure (round the clock for the first 2 days and during daytime for the following 5 days thereafter).

Details of the procedure and possible immediate complications will be recorded in the study register.

Varicose tributaries can be treated with UGFS as described previously at any follow-up visit as necessary. A thigh-length class II compression stocking will be worn for 1 week post-procedure.

### Outcome measures and follow-up

The duration of the follow-up will be five years. The primary outcome measure will be the need for additional treatment of the varicose tributaries during the follow-up, as judged by the patient. The secondary outcome measures will be the cost of treatment and recurrence of varicose disease. Other outcome measures of interest will the length of the procedure time and the impact of treatment on the Aberdeen Varicose Vein Questionnaire (AVVQ) score, the Venous Clinical Severity Score (VCSS), health-related quality of life (the EuroQoL EQ-5D-5L) score, and patient-related outcome measures (PROMs). Data pertaining to PROMs will be collected at 1 year with two questions: “Was the treatment you were given of good quality?” and “Did the treatment you were given meet your expectations?”

In addition, the following data will be collected at the 3-month follow-up visit: pain score based on numeric rating scale (NRS) during the procedure and at three time points post-procedure, the use of analgesics, and the possible procedure-related complications. Patients will also be asked about the duration of sick leave and for their estimate of the appropriate recovery time.

The study leg will be assessed using DUS at each follow-up visit. The protocol for the examination will be identical with the diagnostic DUS described previously under Study setting and patient screening, i.e., the diameter of GSV and SSV will be measured and both veins will be assessed for patency and reflux regardless of whether the vein has been treated or not; the AASV will be systematically assessed only when it has been the target for ablation. Apart from that, it will be assessed as needed, i.e., if there are varicose tributaries that could be connected to the AASV. The treated saphenous trunk will be assessed according to the recommendations and definitions of De Maeseneer et al. [23]. Data on the saphenous trunks and varicose tributaries will be recorded in the study register. During the follow-up visits, patients in both study groups will be able to receive UGFS, if judged necessary by the patient, for the remaining or new tributaries. The additional treatments will be recorded in the study register.

A schematic diagram of the timeline of the study [31] is presented in Fig 1.

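### At follow-up a non-ablated AASV is examined only when tributaries point to it, so detection of AASV reflux can differ by arm and can bias the recurrence comparison if recurrence counts reflux on DUS

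*Protocol article*

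**What the plan says.** Under Outcome measures and follow-up, the article sets two rules for the DUS at each visit. For the GSV and SSV, "both veins will be assessed for patency and reflux regardless of whether the vein has been treated or not". For the third trunk, "the AASV will be systematically assessed only when it has been the target for ablation"; otherwise "it will be assessed as needed, i.e., if there are varicose tributaries that could be connected to the AASV".

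The same paragraph introduces the scan with the words "The protocol for the examination will be identical with the diagnostic DUS described previously". The earlier section, Duplex ultrasonography (DUS), puts the limit elsewhere. It says of every patient that "All three saphenous trunks will be assessed and the diameter, patency, and possible reflux of both the GSV and SSV will be recorded", whereas "The corresponding parameters for the AASV will be registered only when it is the target for ablation". There the AASV is examined in everyone and only the recording is restricted.

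The randomised contrast is in Patient enrolment and randomization: "Patients in group one will be treated with EVLA of the incompetent saphenous trunk without treatment of the varicose tributaries". Group two has the tributaries treated by foam sclerotherapy (UGFS) in the same session. Recurrence of varicose disease is one of two secondary outcomes, and Table 1 asks whether tributary treatment or its timing affects it. The article does not say whether recurrence means visible varicose veins, reflux on DUS, or both.

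**The concern.** What prompts a scan of a non-target AASV is a finding made after randomisation, and one that the allocated treatment is intended to change. Group one leaves the index procedure with its tributaries in place and group two has had them treated. With equal true AASV reflux in both arms, more group one patients may be examined, and so more reflux recorded. The trial is not blinded, and whether a tributary might connect to the AASV is the examiner's judgement. Unequal detection of this kind does not shrink as the sample grows.

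The stake is the recurrence comparison, where the role of tributaries is part of the trial's rationale. A second, distinct issue is that reflux found later in a non-target AASV may have no registered baseline value to show whether it is new.

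**Working it through.** The plan gives no figure on this point, so there is none to reproduce. The check compares the rules and then illustrates size.

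**Rules side by side**

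| Trunk | Diagnostic DUS | Follow-up DUS |
|---|---|---|
| GSV, SSV | assessed and recorded in all | assessed in all |
| AASV, ablated | assessed and recorded | assessed systematically |
| AASV, not ablated | assessed, not registered | assessed only if tributaries could connect to it |

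Only the last row depends on tributaries. It also shows the inconsistency: follow-up is called identical to the diagnostic scan, but follow-up limits assessment where the diagnostic section limits only registration.

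**Illustration of size**

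All inputs are assumptions except 130 patients per group and the 0.05 significance level (Statistical analysis).

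- q = true reflux rate in a non-target AASV, equal in both arms.
- s1, s2 = probability that a refluxing AASV is scanned in group one and group two.
- r = other recurrence, assumed 15% in each arm and independent of AASV reflux.

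Recorded AASV reflux is q × s, so the spurious difference on that component is q × (s1 − s2).

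With q = 15%:
- Scanning 60% vs 20%, unrelated to reflux: 0.15 × 0.60 = 9.0% vs 0.15 × 0.20 = 3.0%, a 6-point gap.
- Scanning 40% vs 20%: 6.0% vs 3.0%, a 3-point gap.
- Scanning closely linked to reflux, 80% vs 70%: 12.0% vs 10.5%, a 1.5-point gap.

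For a composite recurrence outcome, the rate in each arm is 1 − (1 − r)(1 − q × s), so the difference is (1 − r) × q × (s1 − s2). The last column is the chance that a two-sided two-proportion z-test at 0.05 declares a difference when none exists.

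| q | s1 vs s2 | Spurious difference | Rejection rate |
|---|---|---|---|
| any | equal | 0 | 0.05 |
| 5% | 0.5 vs 0.3 | 0.85 × 0.05 × 0.2 = 0.85 points | 0.054 |
| 10% | 0.6 vs 0.2 | 0.85 × 0.10 × 0.4 = 3.4 points | 0.109 |
| 20% | 0.6 vs 0.2 | 0.85 × 0.20 × 0.4 = 6.8 points | 0.263 |
| 20% | 0.7 vs 0.1 | 0.85 × 0.20 × 0.6 = 10.2 points | 0.51 |

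The z-test stands in for the planned Fisher's exact test, and full follow-up of 130 per group is assumed. The last row is an extreme case.

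**Baseline registration**

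Baseline AASV status is fixed before allocation, so leaving it unregistered is balanced between arms in expectation. It blurs new with pre-existing reflux but does not by itself favour an arm.

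**The case against.** The strongest objection is that the outcome is recurrence of varicose disease, not AASV reflux. If recurrence requires new varicose veins, a refluxing AASV without connected tributaries is not an event, and the rule misses little that counts. The operational definition may stand in the full protocol or analysis plan, which are not shown. This objection stands and makes the concern conditional.

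The second is that the trigger is narrower than any leftover tributary: it asks "if there are varicose tributaries that could be connected to the AASV". Veins fed by a refluxing AASV are the ones it is meant to catch, so among patients with AASV reflux the arms may be scanned at similar rates. Eligibility requires tributaries connected to the incompetent trunk, so where the GSV or SSV was the target, many remaining veins in group one need not suggest the AASV. Both arms may also receive UGFS at follow-up visits, which tends to narrow the tributary gap over time. This stands too, and is why the range must reach down towards zero.

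Third, an incompetent AASV is itself a qualifying vein in Table 2, so reflux present at baseline would often make the AASV the target and therefore be registered. The text does not guarantee this, so the gap in the register is possible but not general.

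What survives is that the rule as written ties the examination to something the allocation changes, while the other two trunks are examined unconditionally.

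**Conclusion.** The point holds as a conditional one. For a non-ablated AASV, detection of reflux at follow-up can differ by arm, probably upward in group one. The recurrence comparison can be biased if recurrence counts AASV reflux found on DUS; if new varicose veins are required, the effect is small.

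The size cannot be derived from the document. On assumed inputs it runs from about 1 point or less, when scanning is strongly linked to reflux or similar in both arms, to about 6 points or more, when scanning is 60% vs 20% and unrelated to reflux.

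A reader might infer three stronger things that the document does not support:
- That the recurrence comparison is certainly biased. This depends on a definition the article does not give.
- That the missing baseline AASV record is a further arm bias. It is misclassification expected to be equal in both arms.
- That the primary outcome is compromised. That outcome is the patient's judgement of the need for further tributary treatment, and nothing here shows that it is affected.

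The issue is confined to one trunk, where it was not ablated, within one secondary outcome. It is worth correcting because the correction is cheap.

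**What to change.** Register AASV patency and reflux (yes/no) in every patient at baseline, where the trunk is already examined, and at every remaining follow-up DUS whether or not tributaries are seen. Reconcile the two DUS descriptions so that all four centres follow the same rule.

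For visits already completed without this, keep ablated AASVs in the recurrence comparison, since they are assessed systematically in both arms. Base the rest of the comparison on GSV and SSV reflux plus new tributaries, and report non-target AASV findings separately as incompletely assessed.

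The cost is two register fields and slightly longer scans at visits already scheduled. What was not recorded at past visits cannot be recovered.
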